### 16.1.2 Child-level Analysis

Using the sentinel children, we will construct for each period multivariate models with presence of active trachoma/infection as the outcome. Logistic models of the following form will be built to estimate the effect of the two treatments and their interaction:

$$\text{Log}\frac{\Pr(Y_i = 1)}{\Pr(Y_i = 0)} = \beta_0 + \beta_1 x_{1i} + \beta_2 x_{2i} + \beta_{12} x_{1i}x_{2i} + \gamma_{pi}$$

In this model,  $Y_i$  is an indicator variable for presence of trachoma/infection,  $x_{1i}$  and  $x_{2i}$  are indicator variables for the treatment assignment, high compliance with antibiotic treatment and treatment based on the stopping rule, respectively.  $\beta_1$  is the intervention effect for children living in communities randomized to high antibiotic compliance only,  $\beta_2$  is the intervention effect for children living in communities randomized to treatment based on the stopping rule, and  $(\beta_1 + \beta_2 + \beta_{12})$  for those living in communities randomized to both high compliance and antibiotic treatment based on the stopping rule. The models will include additional covariates ( $\gamma_{pi}$ ) to adjust for initial/previous period trachoma/infection status at community level and other factors thought to be related to the outcome that in spite of randomization were dissimilar at baseline. Because the

outcomes for children living in the same community are likely to be correlated, all standard errors will be corrected to account for that correlation using the Generalized Estimation Equation approach. Since GEE approaches work best when there are a large number of fairly small clusters, we will consider an alternative approach. Using communities as the cluster we will also implement a random effects model allowing the intercept  $\beta_0$  to be  $(\beta_0 + a_i)$  where  $a_i \sim N(0, \sigma^2)$  corresponding to the random variation of the  $i^{th}$  child in a given community. The models are easily implemented using PROC NLMIXED in SAS. We will compare the results of these two approaches to examine the consistency of the inferences.

We plan to evaluate the correlation of clinical trachoma with laboratory evidence of infection in these communities at each survey time point, within treatment arms. It is recognized that in an undisturbed state, there will be more active trachoma than infection, as well as some sub clinical cases of infection. However, following mass treatment there is a pronounced disassociation, as infection declines dramatically with more modest declines in disease rates. Indeed, that is the premise of our contention that a test of infection that indicates low levels may be a better indicator of when to discontinue mass treatment than a clinical indicator. However, over time, clinical trachoma declines as well, although the trajectory is not well described.

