### 1.3 Overall Design

We propose a community-randomized design within each of the three countries, which takes advantage of the level of endemicity to address questions of coverage and frequency. Within these study areas, communities will be randomized (minimum 16 in each arm) to two different coverage targets (80%-89% versus  $\geq 90\%$ ) for three years of mass treatment. In Niger, we will further randomize communities to annual mass azithromycin distribution versus every 6-month distribution. Only children ages 12 and under will receive azithromycin treatment. In The Gambia and Tanzania, we will further randomize communities to yearly mass treatment versus annual mass treatment if warranted by the trachoma infection rates. We will evaluate the efficacy of guiding further mass treatment according to a laboratory test for Chlamydia or WHO guidelines. Where we estimate communities have infection rates less than 5% in sentinel children, or TF rates less than 5%, the community will be “graduated” from further mass treatment and followed for up to three years to look for evidence of re-emergent infection and disease. If rates of infection return to 20% at the 12 or 18-month survey, we will initiate mass treatment again.

Sentinel children randomly selected as cross sectional samples in these communities will be monitored at baseline, 6, 12, 18, 24, 30, and 36 months for infection and clinical disease. The three-year study is in accord with the WHO guidelines for three years of mass treatment followed by a re-survey to determine areas in need of further treatment.

Primary analyses will focus, within countries, on the comparison at three years of trachoma and infection rates in villages randomized to 90% or greater coverage versus less than 90%, and in villages randomized to yearly treatment of everyone versus 6 monthly treatment of children (Niger) or yearly versus in the “stopping rule” arm (Tanzania and The Gambia). Primary analyses will consider the 2 X 2 factorial design, the baseline prevalence, and baseline indicators of environmental hygiene as co-variables and effect modifiers. Secondary analyses will evaluate trachoma and infection in children, adjusting for clustering at the village level.

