## **3) What are differences at 3 years post baseline in rates of trachoma and ocular *C. trachomatis* in communities randomized to yearly mass antibiotic treatment versus a strategy to discontinue treatment (graduate communities), if infection/disease reaches less than 5%? (Tanzania and The Gambia only)**

---

*We hypothesize that the prevalence rates of infection, trachoma will be no different in villages treated for three years versus villages in the arm with the graduation rule at three years in Tanzania and the Gambia.*

Here we use a non-inferiority analysis. A total of 8.06 Tanzanian communities is needed to allow the null hypothesis that the graduation rule is at least 6% inferior to be rejected with a power of greater than 80% using a 2-sided alpha of 5%, and assuming a standard deviation in the 36-month prevalence of 4%. This computation was conducted using the same formula as in hypothesis 1 (see Chow et al, sec. 4.4.1). Note that with a one-sided test with an alpha of 0.05, 80% power is achieved with 7 Tanzanian communities.

A total of 11.9 Gambian communities is needed to allow the null hypothesis that the graduation rule is at least 6% inferior to be rejected with a power of greater than 80% using a 2-sided alpha of 5%, and assuming a standard deviation in the 36-month prevalence of 5%. As before, we used the same formula as in hypothesis 1. For a one-sided test, 80% power is achieved with 10 communities.

We originally computed the sample size for an 8% limit to be considered non-inferior; because for this hypothesis we felt the data would show very low rates of infection (in order to be graduated, the estimate for a community must be 0%) and 6%-7% infection rates at this level would not result in significant re-emergence. However, for consistency sake, we show that we do have 80% power (as opposed to 90% power to detect 8% differences) with the sample size as justified to detect differences as low as 6%.

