## **7.5 Follow-Up Visits**

The first mass treatment is carried out immediately after the baseline survey. Subsequent follow-up visits are at 6, 12, 18, 24, 30, and 36 months from the first mass treatment. The census lists are updated formally every year prior to the 12, 24, or 36 month survey. The 6, 18, and 30 month surveys will use the census lists for the previous survey when drawing new random samples of sentinel children. The window for each survey is +/- two months.

The exact same procedures as stated for the baseline examination visit are to be followed for all subsequent examination visits. In all cases, mass treatment according to treatment arm is to follow immediately after the survey, to ensure that children are not treated prior to the survey.

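### The child-level arm-effect models may adjust for the previous survey's community prevalence, a post-randomisation outcome that would pull the reported effects toward no difference

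*Protocol*

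**What the plan says.** Section 16.1.2 of the protocol sets out the child-level analysis: "we will construct for each period multivariate models with presence of active trachoma/infection as the outcome". The models are built to estimate the effects of the two treatments and their interaction, and the text interprets their coefficients as intervention effects. They will include covariates "to adjust for initial/previous period trachoma/infection status at community level", together with other factors that differ at baseline despite randomisation. The slash joins two different covariates, and nothing says which applies at which survey.

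The surveys are six months apart (section 7.5): "Subsequent follow-up visits are at 6, 12, 18, 24, 30, and 36 months from the first mass treatment".

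Section 1.3 ranks the analyses. For the primary ones: "Primary analyses will consider the 2 X 2 factorial design, the baseline prevalence, and baseline indicators of environmental hygiene as co-variables and effect modifiers". For the child-level ones: "Secondary analyses will evaluate trachoma and infection in children, adjusting for clustering at the village level".

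For the stopping rule, hypothesis 3 in section 4.4.1 expects that "the prevalence rates of infection, trachoma will be no different in villages treated for three years" compared with the graduation arm, and adds: "Here we use a non-inferiority analysis".

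**The concern.** The trial asks what three years of a strategy do to prevalence at 36 months. That is a total effect by original assignment, in line with the intention-to-treat statement in section 16.1. Once the arms have been treated differently, community prevalence at any later survey is part of that effect. A model that holds the previous survey's prevalence fixed removes some of the difference the strategy has already produced, and labels what is left as the intervention effect.

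The bias runs toward no difference. A real benefit of higher coverage or of biannual treatment of children would look smaller than it is. A real disadvantage of stopping would also look smaller, and there the hypothesis is that the arms do not differ, so the error is in the unsafe direction.

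The planned check in section 16.1.2, comparing GEE with a random-effects model, would not reveal this. Both models carry the same covariate and can agree on the same attenuated estimate.

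**Working it through.** **1. The plan's own figures.** Section 4.4.1 sizes hypothesis 3 with a non-central t equation, with 2n − 2 degrees of freedom and non-centrality δ√n / (σ√2). With δ = 6 points, 80% power and two-sided 5%, it gives n = 8.06 for σ = 4% (Tanzania) and 11.94 for σ = 5% (The Gambia). One-sided 5% gives 6.30 and 9.34, rounded up to 7 and 10. The protocol states 8.06, 11.9, 7 and 10, so its figures reproduce. They also show that the margin is an absolute difference in 36-month community prevalence.

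**2. When the previous survey becomes a post-treatment outcome.**

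| Factor | Arms first treated differently | First affected survey | First model whose previous survey is affected |
|---|---|---|---|
| Coverage; biannual (Niger) | First round, right after baseline | 6 months | 12 months |
| Stopping rule | Second round, after the 12-month survey | 18 months | 24 months |

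Sources: section 4.2 (all communities are treated at baseline), section 7.5 (treatment follows the survey), section 8.6 (the 6-month survey decides the second-year round) and Tables 2 and 3. In the 6-month model, baseline and previous period are the same survey.

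In Tanzania the last scheduled round follows the 24-month survey (Table 2). No scheduled treatment falls between 30 and 36 months, so much of a 36-month difference could already be present at 30 months.

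**3. Size of the attenuation, linear analogue.** Let δ30 and δ36 be the arm differences and ρ the within-arm correlation of community prevalence between the two surveys. With equal SDs:

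expected adjusted effect = δ36 − ρ × δ30

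The protocol gives only a baseline-to-36-month correlation (0.5, section 4.4.1), so ρ is an assumption shown as a range. With δ36 = 6 points:

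| ρ (assumed) | δ30 = 6 | δ30 = 3 |
|---|---|---|
| 0.3 | 6 − 1.8 = 4.2 | 6 − 0.9 = 5.1 |
| 0.5 | 6 − 3.0 = 3.0 | 6 − 1.5 = 4.5 |
| 0.7 | 6 − 4.2 = 1.8 | 6 − 2.1 = 3.9 |

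A simulated community-level analysis of covariance (16 v 16 communities, SD 4%) gave mean estimates of 4.17, 2.99 and 1.81 points for the first column and 5.09, 4.47 and 3.92 for the second. Adjusting for baseline instead gave 6.00.

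**4. The logistic form.** Simulation with 16 communities per arm and 100 children each, prevalence 5% v 8% or 11% at both surveys. Assumed inputs were a between-community SD of 0.5 or 0.8 on the logit scale and a 30-to-36-month correlation of 0.5, 0.7 or 0.9. Adjusting for the previous survey left 28% to 71% of the unadjusted log-odds ratio. Adjusting for baseline left it essentially unchanged (for example 0.821 unadjusted, 0.811 adjusted, against 0.581 with the previous survey).

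**The case against.** **The wording also permits the right covariate.** The word initial means baseline, and the same sentence speaks of imbalance at baseline. This stands: the defect is an open choice that admits an invalid covariate, not a commitment to it. But the protocol itself offers the previous-period option for models it says estimate intervention effects, so the text needs correcting whatever a later analysis plan says.

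**The main comparisons are untouched.** Section 1.3 ranks child-level analyses as secondary and names baseline prevalence for the primary ones. The rank tests and mixed model in section 16.1.1 do not condition on the previous survey. The Niger factorial model in section 16.2.4 uses baseline prevalence. This stands too and limits the severity. Section 16.1.2 does sit under the heading for primary outcome analyses, but section 1.3 states the rank.

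**A reader might infer that the plan leads to false non-inferiority for the stopping rule.** If a previous-survey-adjusted community estimate were tested against the 6-point margin, a stopping arm truly 6 points worse would be declared non-inferior in about 18%, 47% or 87% of simulated trials at ρ = 0.3, 0.5 or 0.7 with the full difference present at 30 months (9%, 21% or 45% with half of it). The rate with baseline adjustment is about 2.7%, against a nominal 2.5%. No section specifies that test. The margin is set on absolute community prevalence, and the logistic model has no margin and no non-inferiority decision. Chapter 16 does not rule such a use out, but it does not plan it.

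**A reader might also infer that the adjusted model estimates only the change over the last six months.** It does not. With equal differences at both surveys a change score would be zero, whereas the adjusted effect is 4.2, 3.0 or 1.8 points.

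**High correlations may be implausible.** Each survey draws a new sample of about 100 children. If 4% is the SD of observed prevalence (an assumption), sampling error caps the observed correlation at 1 − (0.05 × 0.95 / 100) / 0.0016 = 0.70 at 5% prevalence and 1 − (0.11 × 0.89 / 100) / 0.0016 = 0.39 at 11%. Allowing for sampling 100 of about 500 children (16,000 over 32 communities, section 4.3), the caps are about 0.76 and 0.51. So ρ = 0.7 is at the upper edge, and 0.3 to 0.5 is the safer range to quote. Attenuation remains substantial there.

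**Conclusion.** The point holds as a should-fix. The child-level models may condition the arm effects on a post-randomisation outcome, from the 12-month model on for coverage and biannual treatment and from the 24-month model on for the stopping rule. Doing so biases those effects toward no difference. A true 6-point difference present at both 30 and 36 months would be reported as 4.2 to 3.0 points at ρ = 0.3 to 0.5, and as 1.8 points at ρ = 0.7. The direction of the bias follows from a positive correlation and a 30-month difference of the same sign. Its size rests on the assumed ρ, on equal SDs and on how much of the difference exists by 30 months, none of which the protocol gives.

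For the stopping rule the direction is anti-conservative. A false non-inferiority conclusion would follow only if this secondary, margin-free model were used for that inference, and the community-level comparisons are not affected.

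**What to change.** In section 16.1.2, delete the previous-period alternative and add one sentence: every model from which an arm effect is reported, at every survey, adjusts for baseline (pre-treatment) community prevalence only. This agrees with section 1.3, with the baseline correlation behind the sample size in section 4.4.1 and with the Niger factorial model in section 16.2.4.

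If previous-survey status is wanted for questions of transmission or re-emergence, put it in a separately labelled transition analysis from which no arm effect is reported. Section 16.2.3 already plans a re-emergence analysis of children free of infection or disease at a previous round.

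The cost is a few words of text. No data collection changes, and no planned precision is lost, because the sample-size simulation already assumes the baseline correlation.

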### 4.3 Communities and Sentinel Children

In order to determine the impact of our treatment arms on trachoma and infection, we will randomly sample a sentinel group of up to 100 children within randomly selected communities. *We define communities as the smallest population unit for which health services are organized and trachoma control programs are implemented.* These communities vary in size between countries. In Niger, we will use Grappes, comprised of 250- 600 people, as communities. In The Gambia, we will use Census Enumeration Areas, of population size 600-800 as communities. In Tanzania, we will use mtaas or clusters of mtaas, which average around 1200 population. As described below, we plan to have 8 communities in each cell of the Tanzanian arms, and 12 communities in each cell of the Nigerien and The Gambian arms. We need multiple communities to have a stable estimate of the impact of the treatment arm.

We also need a large enough sample **within** the communities for The Gambia and Tanzania, in order to be able to determine if mass treatment is to cease, based on our infection and disease rules for stopping. The universe of children being sampled differs for each of the country settings, as it relates to the size of the community. In Tanzania, of the potentially 16,000 children who form the universe of the sample, 3200 will be randomly selected, or one in five. In The Gambia, 48 Census Enumeration Areas (CEA) will be randomly selected of the 114 to serve as sentinel communities. With about 700 persons total and 175 children in the eligible age range, the total universe for this sample is 8400 children. 4800 children will be randomly selected at each survey, for a slightly higher than 1/2 chance of selection. In Niger, the study area is comprised of 6 Centre de Santé Intégrés (CSI) or integrated health centers composed of 235 grappes (roughly comparable to a village with an

average size of 375 people). 48 of these grappes were randomly selected to serve as study communities (8 grappes from each of the 6 CSI), with up to 100 children and 40 randomly selected adults included in each round. Note, that there is no stopping rule in Niger, and thus a sample size smaller than 100 children is not an issue.

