For this trial, we propose to monitor the changes in prevalence and infection over time according to treatment arm. For this, simple cross-sectional samples of up to 100 children ages 0 to 5 years within the community at specified times are sufficient. This sample will enable us to determine the effect of treatment after each round, and if treatment is to be stopped in the communities of The Gambia and Tanzania. This sample will not be followed longitudinally, and at each sampling time, a new random sample will be drawn. To support the sampling, a census update will be performed yearly.

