#### 16.2.4 Specific Analyses for the Niger site

The following analyses are planned for the Niger site (UCSF). All tests are two-sided with an alpha level of 0.05.

- In the annual azithromycin arm, we propose to compare resistance levels in pneumococcus from nasopharyngeal swabs taken at baseline to resistance levels at 36 months, to determine whether or not resistance levels have risen. This will be conducted using the Wilcoxon signed rank test on the differences (thus accounting for pairing). In all uses of linear regression or linear models with prevalence as the outcome, we propose to use the square root or fourth root transformation to stabilize the variance.
- In the biannual children arm, we propose the same analysis. Specifically, we propose to compare resistance levels in pneumococcus from nasopharyngeal swabs taken at baseline to resistance levels at 36 months, to determine whether or not resistance levels have risen. This will be conducted using the Wilcoxon signed rank test on the differences (thus accounting for pairing).
- At 36 months, we propose to compare the resistance levels in pneumococcus from nasopharyngeal swabs between two arms: the annual arm and the children biannual arm. We wish to determine whether or not treating children biannually causes more resistance than treating everyone annually. We propose to use the Wilcoxon rank sum test (there is no pairing).
- We propose to compare the chlamydia infection levels (from PCR taken from conjunctival swabs) in adults at baseline to the infection levels in adults at 36 months, in communities in the biannually treated arms. Because only children are treated, changes in adult prevalence are attributable to herd protection. The primary comparison will disregard the intended coverage target assignments and compare all villages using the Wilcoxon signed rank test (one-sample test on the differences, thus accounting for pairing). Supplemental analyses will (a) be conducted separately on the 90+% coverage arm, and (b) be conducted using a linear model with the outcome variable being the 36 month adult prevalence, and predictors being the baseline prevalence in adults, and coverage. Baseline prevalence in children may also be used as a predictor instead of baseline prevalence in adults.

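### The child-level GEE has few, large clusters, and comparing it with a second model does not correct its standard errors or settle which result stands

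*Protocol*

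**What the plan says.** Section 16.1.2 fits, at each survey, a logistic model for the individual child. It contains both randomised factors, their interaction, and covariates that include earlier community-level trachoma or infection. On clustering it says that "all standard errors will be corrected to account for that correlation using the Generalized Estimation Equation approach". It names no small-sample correction, reference distribution or degrees of freedom. It then concedes the limitation: "Since GEE approaches work best when there are a large number of fairly small clusters, we will consider an alternative approach". The alternative is a random community intercept fitted in PROC NLMIXED, after which "We will compare the results of these two approaches to examine the consistency of the inferences".

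Section 4.3 plans "8 communities in each cell of the Tanzanian arms, and 12 communities in each cell of the Nigerien and The Gambian arms". The surveys take "simple cross-sectional samples of up to 100 children ages 0 to 5 years" in each community. Section 1.3 ranks the child-level analysis as secondary. Section 16.1 describes the community-level and child-level analyses as complementary.

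**The concern.** The section identifies the right problem: GEE standard errors rely on many clusters, and here there are few clusters, each large. The remedy does not act on it. Fitting another model leaves the GEE standard errors as they were. The second model is also a large-sample method with the same few communities. If the two agree, both may be too optimistic. If they disagree, no rule decides between them.

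The interaction sharpens this. As section 16.1.2 defines them, the coefficients for coverage and for the second factor are effects within one level of the other factor. Each therefore compares 8 with 8 or 12 with 12 communities, not 16 with 16 or 24 with 24. At stake are child-level p-values and confidence intervals that look more certain than the number of communities allows.

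**Working it through.** **Inputs from the Protocol.** Communities per cell: 8 (Tanzania), 12 (Niger). Children per community: up to 100. Standard deviation of 36-month community prevalence (section 4.4.1): 4% for Tanzania and 5% for the smaller communities. Correlation of baseline with 36 months: 0.5. Nominal level: two-sided 5%; for Niger, "All tests are two-sided with an alpha level of 0.05".

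**Assumptions.** The Protocol gives no common null prevalence, so 2% to 20% was run. Section 4.4.1 projects about 2% and 13% for high and low coverage. The standard deviations were applied to the underlying community prevalence, taken as beta distributed, with binomial sampling of 100 children. "Default GEE" means an uncorrected sandwich variance with a normal critical value.

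**1. The plan's own figure.** Section 4.4.1 solves the non-central t equation with 2n-2 degrees of freedom and non-centrality d√n/(s√2). With d = 6%, two-sided 5% and 80% power:
- s = 4% gives n = 8.06 (stated: 8.06)
- s = 5% gives n = 11.94 (stated: 11.9)

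These reproduce. The design stage therefore uses a t reference with between-community degrees of freedom, which section 16.1.2 does not carry over.

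**2. Analytic approximation.** With m equal clusters in a cell, the uncorrected sandwich divides by m where m-1 is needed. The test then rejects when |t| > 1.96√((m-1)/m).
- Cell contrast, m = 8: 1.96√(7/8) = 1.833; P(|t14| > 1.833) = 8.8%
- Cell contrast, m = 12: 1.96√(11/12) = 1.877; P(|t22| > 1.877) = 7.4%
- Main effect taken from the model with interaction, 28 and 44 df: 7.7% and 6.7%
- Two groups without interaction, 16 v 16: 1.96√(15/16) = 1.898; 30 df: 6.7%
- Two groups without interaction, 24 v 24: 1.96√(23/24) = 1.919; 46 df: 6.1%

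**3. Simulation under the null** (40,000 trials per setting, no covariate), rejection rate of the coverage coefficient:

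| Null prevalence | 8 per cell, SD 4% | 12 per cell, SD 5% |
|---|---|---|
| 5% | 10.2% | 8.7% |
| 10% | 8.9% | 7.8% |
| 13% | 9.0% | 7.3% |
| 20% | 8.5% | 7.4% |

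A separate run gave 8.6-10.2% and 7.4-9.1% over the same range. At 2% prevalence the rate is about 17%. Two-group main effects at 5-20% prevalence run at 6.6-7.6% (16 v 16) and 6.0-6.9% (24 v 24). Main effects taken from the interaction model run at 7.6-9.3% and 6.6-8.4%.

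Adding a baseline-prevalence covariate (mean 20% and SD 10% assumed; 6,000 trials) gives, at 5% and 10% prevalence, 10.4% and 10.3% with 8 per cell, and 9.9% and 8.2% with 12.

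**4. The plan's remedy.** A maximum-likelihood random-intercept model with the covariate and (communities - 1) degrees of freedom stood in for NLMIXED. About 700 trials were run, so the Monte Carlo error is about one point.

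| Setting | Random intercept rejects | Either model rejects | Both reject |
|---|---|---|---|
| 8 per cell, 5% | 9.9% | 14.5% | 8.2% |
| 8 per cell, 10% | 5.8% | 10.7% | 5.3% |
| 12 per cell, 10% | 7.3% | 10.0% | 6.4% |

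The error rate depends on how disagreement is handled, which the plan does not state.

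**5. With a correction.** In a cell of m equal clusters each has leverage 1/m. Kauermann-Carroll therefore multiplies the variance by m/(m-1), and Mancl-DeRouen by its square. The first, with t on 2(m-1) degrees of freedom, gives for the cell contrast 6.0% and 5.1% (8 per cell; prevalence 5% and 10%) and 6.1% and 5.3% (12 per cell). Mancl-DeRouen with t, at 5% prevalence and SD 4%, gives 4.6% (8 v 8) and 5.0% (12 v 12). At 2% prevalence about 9-13% remains.

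**The case against.** The strongest reply is that section 16.1.2 never says which sandwich estimator or reference distribution will be used, and a statistical analysis plan could add the correction. A reader might infer that the Protocol specifies the ordinary sandwich. It does not; that is only the default reading. What survives is narrower. The section raises the few-cluster problem and fixes a remedy for it, and that remedy does not work.

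The second reply concerns rank. Section 1.3 makes the analysis secondary. The community-level tests in section 16.1.1, the sample-size calculations and the Niger linear models in section 16.2.4 do not use this GEE. This stands. A reader might infer that the trial would declare false differences about twice as often as stated. The documents do not support that: the figures apply to this analysis only, and the two-group comparisons on which the design is powered run at about 6-7.5% at prevalence of 5% or more.

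A reader might also infer that non-inferiority limits would be too tight. Section 4.4.1 sets its margins (8% and 6%) as absolute differences in community prevalence, whereas this model yields log odds ratios. No odds-ratio margin is set, and no non-inferiority test is assigned to this model.

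Finally, the authors disclosed the limitation themselves. That is to their credit, but disclosure does not correct the standard errors.

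**Conclusion.** The point holds for a secondary analysis. If the GEE is run at its default, type I error at nominal 5% is about 9-10% (8 per cell) and 7-9% (12 per cell) for the cell-level coefficients, and about 6-7.5% for two-group main effects. The baseline covariate can take the 12-per-cell figure to about 10%. These figures rest on an assumed null prevalence of 5-20%, the Protocol's standard deviations and 100 children per community. Near 2%, cell contrasts reach about 17%. The planned comparison with a random-intercept model does not remove the excess and leaves the governing result undefined.

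The figures for 12 per cell should not be carried over to The Gambia. Section 4.3.3 assigns one district to each cell, so its enumeration areas are not independently randomised.

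**What to change.** In section 16.1.2:
- For all GEE results, use a bias-corrected sandwich (Kauermann-Carroll or Mancl-DeRouen) with a t reference and between-cluster degrees of freedom. Without covariates these are 14 or 22 for cell contrasts and 28 or 44 for main effects and interaction in the model as written.
- Use between-cluster degrees of freedom for the random-effects model too.
- Name in advance one governing child-level result and treat the other as a sensitivity analysis.
- Where prevalence is near 2%, let the community-level test govern, because the correction is not enough there.
- Do not present this as a remedy for The Gambia.

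The cost is a software option, a few sentences and wider intervals. With Kauermann-Carroll, cell-contrast intervals widen by √(8/7) × 2.145/1.96 = 1.17 (8 per cell) and √(12/11) × 2.074/1.96 = 1.11 (12 per cell). Two-group main effects widen by √(16/15) × 2.042/1.96 = 1.08 and √(24/23) × 2.013/1.96 = 1.05. No new data are needed.
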